##### Social contacts

The Register of Social Networking (developed and used in the previous study by Vázquez and colleagues [11]) will be used to assess the number of participants' weekly social contacts. In this instrument the participants are asked to report the number of people they have had contact with daily.

##### Self-efficacy

The self-administered General Self-Efficacy Scale (GSES) [33] (Spanish version of Baessler and Schwarzer [34]) will be used to evaluate the self-efficacy of the caregivers. Through its 10 items, each participant assesses the feeling of personal competence to handle difficult situations on a Likert scale ranging from 1 (false) to 4 (true) with higher scores indicating greater self-efficacy. The internal consistency of the Spanish version is .81.

##### Dropout and treatment adherence

We will construct a registry of dropouts from each group over the duration of the study. In addition, treatment adherence will be assessed by recording the number of sessions each caregiver attends and whether they complete homework assignments.

##### Satisfaction with the service received

We will evaluate the participants' self-reported satisfaction with the services received using the Client Satisfaction Questionnaire (CSQ-8) [35] (Castilian version of Vázquez and colleagues [36]). It has 8 items with 4 possible answers and a total score ranging from 8 to 32, with a higher score indicating higher satisfaction. Its internal consistency ranges between .83 and .93 [37].

### Data management

Participant files are to be stored in numerical order and stored in a secure and accessible place and manner. Participant files will be maintained in storage for a period of 5 years after completion of the study. All data will be entered in a database; in which no individuals can be identified. Range checks and consistency checks against data already stored in the database will be made. All forms, audios and hardware related to study data will be kept in locked cabinets. Access to the study data will be restricted. A password system will be utilized to control access. A complete back up of the primary database will be performed twice a month. All reports will be prepared such that no individual subject can be identified.

### Statistical analyses

All analyzes will be conducted in accordance with the principle of intention to treat. All participants will be analyzed in the group to which they were assigned. The most conservative approach for attrition will be adopted by considering dropouts as a treatment failure (i.e., a major depressive episode was triggered) and by replacing missing data with the corresponding baseline scores. Cumulative incidence rates of depression for all three groups will be calculated to examine the efficacy of the interventions on prevention of major depressive episodes. The relative risk (RR) and number needed to treat (NNT) will be calculated according to the formulas proposed by Guyatt et al. [38]. Also, the time it takes for the participants to suffer a major depressive episode will be analyzed using a survival analysis. The effect of the interventions on depressive symptoms will be examined by using mixed factorial analysis of variance (ANOVA) tests with repeated measures. To examine the relationship of the received interventions and depressive symptoms as mediated by change in automatic negative thoughts, self-efficacy, and reinforcement, we will utilize the method recommended by Baron and Kenny [39]. The acceptability and adherence to interventions will be examined by using the Chi-Square test to compare the percentages of dropouts and the Student *t*-test for independent samples will be used to compare session attendance and homework completion. The level of participant satisfaction with the interventions will be analyzed with frequency distribution of each item in the CSQ-8, and we will compare results across both conditions using the Student *t*-test for independent samples. All analyzes will be conducted using SPSS for Windows, version 20.0.

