Moreover, the most effective interventions to reduce depressive symptoms and prevent depression are multicomponent cognitive-behavioral programs [8, 16]. Specifically, in an indicated prevention intervention, Vázquez and colleagues [11] applied cognitive techniques to change thought patterns (e.g., double-standard technique, priming) and behavioral techniques to active behaviors (e.g., pleasant activities planning, reinforcement). They found a significant reduction in the incidence of depression (1.1 % vs. 12.2 %) and depressive symptoms (Cohen's *d* = 1.05) when compared to the control group. Using a dismantling strategy could help identify the contribution of behavioral activation techniques to the therapeutic change. As a result, this can contribute to the improvement of the prevention program and to greater efficiency. The behavioral activation techniques should play an essential role because assuming the caregiver role entails a number of behavioral changes related to leisure and recreation, family life and work that may involve a loss of positive reinforcement and an increase in aversive experiences, factors relevant to the development of depression [17]. In fact, a link between the shortage of leisure activities for caregivers and depressive symptoms has been previously demonstrated [18]. Furthermore, previous research [19–22] comparing antidepressant medication, cognitive techniques aimed at the automatic thoughts and underlying schemes, and behavioral activation techniques have shown that behavioral interventions are sufficient to effectively and efficiently treat depression.

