### Sample size

Based on previous studies of indicated prevention of depression in caregivers [10, 11, unpublished paper of Note 1] and studies that have administered therapies for depression by phone (see [13]), we estimate that a sample size of 56 participants per group (168 in total) will be sufficient to detect a difference of 19 % in the rates of incidence of depression episodes between experimental and control conditions, assuming α = .05 and a power (1 - β) of .80. However, assuming an attrition rate of 5-8 %, we estimate that the sample size for each of the groups should be approximately 60 subjects (180 in total).

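### Counting every dropout in any arm as a depressive episode is not the most conservative rule, and it does not match the attrition allowance behind 60 per arm

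*Protocol article*

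**What the plan says.** The primary outcome is major depression by SCID-CV (Outcomes, Table 1). Its analysis is described in Statistical analyses: "Cumulative incidence rates of depression for all three groups will be calculated to examine the efficacy of the interventions on prevention of major depressive episodes". RR and NNT follow, and "the time it takes for the participants to suffer a major depressive episode will be analyzed using a survival analysis".

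The dropout rule stands in the same section: "The most conservative approach for attrition will be adopted by considering dropouts as a treatment failure (i.e., a major depressive episode was triggered"). It makes no distinction between arms, and the protocol keeps a dropout record for each group. Scale scores are handled separately, "by replacing missing data with the corresponding baseline scores"; this point concerns only the episode outcome.

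The Sample size section calls 56 per group "sufficient to detect a difference of 19 % in the rates of incidence of depression episodes between experimental and control conditions". The type I error is set at 0.05 and the power at 0.80. The number is then raised to about 60 per group, "assuming an attrition rate of 5-8" %. The section does not give the two rates behind the 19 points. The only arm-level incidences in the article come from an earlier face-to-face trial, cited in Background: "a significant reduction in the incidence of depression (1.1 % vs. 12.2" %).

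**The concern.** A missing-data rule deserves to be called most conservative only if no reasonable alternative is harder on the intervention. This one is hard on the intervention for active-arm dropouts but generous for control dropouts, each of which becomes a control event. If the usual-care arm loses more people, the rule creates benefit. If the active arms lose more, it hides benefit.

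There is also a mismatch with the sample size. Dividing 56 by the retained fraction protects power when dropouts are left out. When they stay in as events, both rates rise and the difference shrinks, so the extra four per arm do not do the job intended. What is at stake is the meaning of the primary estimate, the direction of its bias and the stated 80% power.

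**Working it through.** **Inputs.** From the article: difference 19 points, α = 0.05, power 0.80, 56 raised to 60 per arm, attrition d = 5-8%, earlier-trial incidences 1.1% and 12.2%. Assumed: a two-sided test, the split of the 19 points into two arm rates, and any dropout rate outside 5-8%.

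**1. The plan's own figure.** With active rate 6%, control rate 25% and mean 15.5%:

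n = [1.960·√(2·0.155·0.845) + 0.842·√(0.06·0.94 + 0.25·0.75)]² / 0.19² = 55.8, so 56.

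The allowance is 56/0.95 = 58.9 and 56/0.92 = 60.9, so about 60. Both stated numbers are therefore attainable, and the allowance is the one for an analysis that omits dropouts. Other calculation methods reach 56 at other active rates: about 2.7% with continuity correction, 7% with the arcsine or unpooled formula, and 11.4% one-sided.

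**2. Effect of the rule.** With true incidence p and dropout d, the analysed rate is q = d + (1 − d)p. With equal dropout, the difference becomes (1 − d) × 19 points: 18.05 at 5% and 17.48 at 8%. For 6% vs 25%, the analysed rates are 10.7% vs 28.75% at 5% and 13.5% vs 31.0% at 8%. RR moves from 0.24 to 0.37 and 0.44.

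**3. Power.** Exact enumeration of the uncorrected two-sided chi-square test over two binomials. The rule keeps 60 per arm; leaving dropouts out gives 57 or 55 per arm.

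| True rates | Attrition | Rule, 60 per arm | Dropouts left out |
|---|---|---|---|
| 6% vs 25% | 5% | 71.6% | 83.5% |
| 6% vs 25% | 8% | 65.0% | 81.9% |
| 1.1% vs 20.1% | 5% | 81.5% | 96.7% |
| 1.1% vs 20.1% | 8% | 72.1% | 96.1% |

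The second pair of rates does not reproduce n = 56; it joins the earlier trial's active incidence to the planned 19 points. By normal approximation, the continuity-corrected calibration (2.8% active) gives 76.2% falling to 68.3%, and the one-sided one (11.5%) gives 74.4% falling to 69.6%.

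**4. Real and imputed episodes in an active arm of 60.** Real = 60(1 − d)p; imputed = 60d.

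| Active incidence | Real, d = 5% / 8% | Imputed, d = 5% / 8% |
|---|---|---|
| 1.1% | 0.6 / 0.6 | 3.0 / 4.8 |
| 6% | 3.4 / 3.3 | 3.0 / 4.8 |
| 11.5% | 6.6 / 6.4 | 3.0 / 4.8 |

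The two are equal when p = d/(1 − d), which is 5.3% at d = 5% and 8.7% at d = 8%.

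**5. Unequal dropout.** With no true effect, the analysed difference (control minus active) is (1 − p)(d_control − d_active). It favours the intervention whenever the control arm loses more. Type I error, same enumeration, 60 per arm:

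| Dropout active / control | p = 1.1% | p = 5% | p = 12.2% |
|---|---|---|---|
| 5% / 8% (planned range) | 9.1% | 7.7% | 6.4% |
| 3% / 10% (assumed) | – | 20.7% | 13.7% |

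In the second row, nearly all the rejections favour the intervention.

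With a true 6% vs 25%, dropout of 5% active and 8% control gives 31.0 − 10.7 = 20.3 points, above the true 19. The reverse gives 28.75 − 13.5 = 15.2 points.

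**6. Is it the most conservative rule?** If active dropouts count as episodes and control dropouts as none, the difference is (1 − d) × 19 − d × 100 points: 13.0 at 5% and 9.5 at 8%. The planned rule leaves 18.05 and 17.48. A harsher rule exists even when dropout is equal.

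**The case against.** The rule is prespecified and applied alike to all arms, and with equal dropout it pulls RR toward 1. Planned attrition is low, retention measures are described under Design, and dropout percentages will be compared between groups. Censoring has its own weakness: if worsening mood causes withdrawal, dropout is informative. All this is fair. But comparing dropout would reveal an imbalance without correcting it, and none of it rescues the label or the sample-size allowance.

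Four stronger readings are tempting, and the article does not support them.

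- *That imputed episodes would outnumber real ones in the active arms.* This holds at 1.1%, but that is one earlier trial's result, not a stated planning rate. At 6% the two are about equal, and at 11.5% real episodes are more numerous.
- *That power must fall below 80%.* At 1.1% vs 20.1% with 5% attrition it is 81.5% by exact enumeration (79.7% by normal approximation). Nor is 1.1% vs 12.2% a fair test of the power statement: that gap is 11.1 points, and 56 per arm has only about 72% power for it before any imputation.
- *That unequal dropout would seriously inflate false positives.* Within 5-8% the inflation is modest. The 14-21% figures need a gap that the article does not foresee.
- *That the survival analysis certainly mixes dropout with depression.* The general rule can be read that way, but the article does not say how dropouts enter that analysis, and an unseen analysis plan may settle it.

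**Conclusion.** The concern holds in bounded form. Two parts need no assumption about the arm rates: the rule is not the most conservative, because control dropouts counted as events favour the interventions; and the step from 56 to 60 per arm fits an analysis without dropouts, not the one described. The bias can run either way, and the primary estimates would describe a composite of dropout and depression.

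The size depends on unstated rates. At 6% vs 25%, power is about 72-65% over 5-8% attrition, 12 to 17 points below the same trial with dropouts left out. At 1.1% vs 20.1% it is about 82-72%. A shortfall against 80% is likely but not certain. False-positive inflation is about 6-9% at the extremes of the planned attrition range, and serious only with a wider gap. Because the rule acts on the primary endpoint and is cheap to change, it should be changed before the data are analysed.

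**What to change.** In Statistical analyses:

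- Make the primary analysis time to first SCID-diagnosed episode, with dropouts censored at their last completed SCID, and derive 12-month Kaplan-Meier cumulative incidence, RR and NNT from it. Alternatively, use multiple imputation with baseline and last available CES-D as predictors.
- Keep dropout counted as an episode in all arms as a sensitivity analysis, beside a true worst case: active dropouts as episodes, control dropouts as no episode.
- Delete the claim that the present rule is the most conservative.

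In Sample size: state the two arm rates behind the 19 points and make the power statement match the dropout handling used. With censoring or imputation as primary, the step from 56 to 60 is broadly coherent, so no extra participants need follow. If the present rule stayed primary, 80% power at 5.8% vs 24.8% (also a reproduction of n = 56) would need about 75 per arm at 5% attrition and 88 at 8%, by normal approximation.

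The cost is a change of wording. The downside is that censoring or imputation assumes dropout is ignorable given the observed data; the sensitivity analyses show how far the result depends on that.

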### Outcomes

Throughout the study, we will collect information on sociodemographic characteristics and situation of care, major depressive episode and other mental disorders, depressive symptoms, the mediating variables (negative thoughts, self-efficacy, reinforcement, social contacts), adherence to treatment, dropouts and satisfaction with the interventions (see Table 1). The self-administered instruments will be mailed to participants to complete them in their homes. The hetero-administered ones will be administered via telephone by trained evaluators who are unfamiliar with the purpose of the study, the interventions that will be administered and the random assignments into each group. Training of the evaluators will consist of 15 h of theoretical and practical workshops and role-playing on the instruments of measurement and evaluation strategies by one of the study investigators who has over 20 years experience in evaluation.

**Table 1 Tab1:** Overview of measures

Instrument	Intervention phase	Format
Participant characteristics		
Socio-demographic and care situation characteristics	Pre-treatment	Self-administered
Primary outcome		
Major depression: SCID-CV	Pre-treatment, Post-treatment, 1-, 3-, 6- and 12-month follow-ups	Hetero-administered
Secondary outcomes		
Depressive symptoms: CES-D	Pre-treatment, Post-treatment, 1-, 3-, 6- and 12-month follow-ups	Self-administered
Automatic negative thoughts: ATQ-N	Pre-treatment, Post-treatment	Self-administered
Reinforcement: EROS	Pre-treatment, Post-treatment	Self-administered
Register of social networking	Pre-treatment, Post-treatment	Self-administered
Self-efficacy: GSES	Pre-treatment, Post-treatment	Self-administered
Dropout and treatment adherence	During the intervention, Post-treatment, 1-, 3-, 6- and 12-month follow-ups	Hetero-administered
Satisfaction with the service received: CSQ-8	Post-treatment	Self-administered

*Note*: *SCID-VC* Structured Clinical Interview for DSM-IV Axis I Disorders, Clinician Version, *CES-D* Center for Epidemiologic Studies Depression Scale, *ATQ-N* Automatic Thoughts Questionnaire, *EROS* Environmental Reward Observation Scale, *GSES* General Self-Efficacy Scale, *CSQ-8* Client Satisfaction Questionnaire

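### Baseline replacement sets mediator and CES-D change to zero together for anyone missing at post-treatment, a small anti-conservative bias in the mediation analysis at planned attrition

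*Protocol article*

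**What the plan says.** All points are from the protocol article.

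- **Scope (Statistical analyses).** The section opens with "All analyzes will be conducted in accordance with the principle of intention to treat".
- **Missing scores (same section).** Dropouts count as failures for the depression endpoint. Scores are handled "by replacing missing data with the corresponding baseline scores". The article describes the pair of rules as the most conservative option and names no exception.
- **Mediation (same section).** The analysis concerns "depressive symptoms as mediated by change in automatic negative thoughts, self-efficacy, and reinforcement", by the Baron and Kenny method.
- **Collection (Outcomes and Table 1).** "The self-administered instruments will be mailed to participants to complete them in their homes". The CES-D, ATQ-N, EROS and GSES are all of this type. The three mediators are measured only before and after treatment; the CES-D is also measured at the four follow-ups.
- **Attrition (Sample size).** The target is "56 participants per group (168 in total"), raised to about 60 per group "assuming an attrition rate of 5-8" %.
- **Expected change (Background).** Both interventions are expected to reduce symptoms and to act through the mediators. The earlier face-to-face trial is cited with d = 1.05 on symptoms.

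**The concern.** Replacing a missing score with baseline usually shrinks a treatment difference, which is why it is called conservative. A mediation analysis also estimates the slope of symptom change on mediator change within arm, and there the rule can work the other way. The four questionnaires are mailed, so a person who does not return the post-treatment forms will usually lack all of them. The rule then places that person at exactly (0, 0), while the others cluster around their mean change on both. Mixing the two clusters yields a slope even where mediator and outcome are unrelated given arm.

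Identifying the mediators is one of the two stated objectives, and the secondary hypotheses assign different mediators to the two interventions. The same people produce the artefact for all three mediators, so it would also tend to make those mediators look alike.

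**Working it through.** **1. The plan's own figure.** 56 / (1 − 0.05) = 58.9 and 56 / (1 − 0.08) = 60.9, so about 60 per group is reproduced. At 60 per arm, 5-8 % missing is 3 to 4.8 people, and 15-20 % is 9 to 12.

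**2. Mechanism.** Let p be the share missing at post-treatment, and mM and mY the mean changes of the others, with no true association within arm. Setting the missing changes to zero gives, within that arm,

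covariance = p(1 − p) × mM × mY.

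If either mean change is zero, no slope arises.

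**3. Assumptions.** Not in the article: scores with SD 1, pre-post correlation 0.6 (so change variance 2 × (1 − 0.6) = 0.8), missingness at random and equal in both arms, and these mean changes (intervention / control):

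- Larger: mediator 0.8 / 0.2 SD; CES-D 1.35 / 0.30 SD. The CES-D difference is 1.05, matching the cited d.
- Smaller: mediator 0.6 / 0.1 SD; CES-D 0.8 / 0.3 SD.

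**4. Expected false slope.** Adjusting for arm, larger changes, p = 0.08:

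- Mean product of changes: (0.8 × 1.35 + 0.2 × 0.30) / 2 = 0.57.
- Covariance: 0.08 × 0.92 × 0.57 = 0.0420.
- Mediator variance: 0.92 × 0.8 + 0.0736 × (0.64 + 0.04) / 2 = 0.761.
- Slope: 0.0420 / 0.761 = 0.055. Simulation gave 0.056-0.058.

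Smaller changes: mean product 0.255, covariance 0.0188, variance 0.750, slope 0.025.

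**5. Rejection rate of the 5 % path test.** True path zero, two arms of 60, regression of CES-D change on arm and mediator change, 4,000-6,000 simulated trials per setting. Ranges span repeated runs.

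| Missing at post-treatment | Larger changes | Smaller changes |
|---|---|---|
| 0 % | 5.4-5.8 % | 4.6 % |
| 3 % | 5.4 % | 5.3 % |
| 5 % | 6.1-7.6 % | 5.5-6.4 % |
| 8 % | 8.8-10.0 % | 6.5-6.8 % |
| 15 % | 18.5-20.1 % | 9.4 % |
| 20 % | 26.8-28.7 % | 11.7 % |

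With post-treatment scores adjusted for baseline instead of change scores, the larger-change rates are somewhat higher: 7.9 % and 12.4 % at 5 % and 8 % missing, 24.3 % and 33.5 % at 15 % and 20 %.

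**6. Dependence on the assumed changes.** With 0.5 SD on both variables in the intervention arm and none in control, the rate at 5-8 % missing is 4.6-5.8 % across both models, so negligible. With 1.1 and 1.35 SD in the intervention arms and 0.3 SD in control, it reaches 16.4 % at 8 % missing (two arms, baseline-adjusted) or 17.5 % (three arms, change scores).

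**7. Where the artefact is absent or slight.**

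- Lost only after post-treatment, with a follow-up CES-D as outcome: mediator change is observed and only CES-D change is set to zero. A true slope of zero stays at zero; a true 0.50 falls to 0.46 at 8 %.
- A true association exists and both scores are missing: 0.50 becomes 0.51-0.54 at 5-8 %.

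**The case against.** Four points can be made for the plan.

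- **Scope.** The rule is stated in connection with attrition, before any analysis is named, and the article never says that it governs the mediation regressions. An unseen analysis plan may treat them separately. This tempers the point, but the section opens by covering all analyses and makes no exemption, so the natural reading includes mediation.
- **The 5-8 % covers the whole trial to 12 months.** Post-treatment follows five weekly sessions, so fewer people may be missing by then; at 3 % the test is near nominal. This stands. Against it, unreturned mailed forms could exceed formal dropout, but the article gives no rate.
- **The rule is not uniformly favourable to mediation.** It also shrinks the arm-to-mediator effect by the factor (1 − p). This stands.
- **A true path of exactly zero is the least favourable case.** This also stands: where a real association exists, the inflation is slight.

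A reader might infer that a false mechanism would be reported, or that every candidate mediator is pushed to significance. The documents do not support that. At 8 % missing with the larger changes, the false indirect effect is about 0.058 × (0.8 − 0.2) × 0.92 = 0.032 SD, against an assumed total effect of 1.05 SD. All Baron and Kenny steps are then falsely met in 7.6-8.8 % of simulated trials, against 2.6 % with nothing missing. With the smaller changes the figure is 2.6-3.4 % at 2-8 % missing. The high rates need 15-20 % missing at post-treatment, which appears nowhere in the article.

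**Conclusion.** The point holds as a small one. For the mediator-to-outcome path, the rule called conservative is anti-conservative for anyone already missing at post-treatment. At the planned 5-8 %, all by post-treatment, a nominal 5 % test of change scores rejects about 5-10 % of the time under the assumed changes, and up to about 12 % with baseline-adjusted scores. It becomes material, about 10-35 %, only at an assumed 15-20 % missing.

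This rests on the four forms going missing together, non-zero average change on both mediator and CES-D, and no true within-arm association. The article supports the first through its collection method and the second through its hypotheses; it gives no mediator changes. Changing the mediation test would not remove the bias, because it lies in the filled-in data. The primary outcome is not affected.

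**What to change.** Add a sentence to the Statistical analyses section exempting the mediation analysis from baseline replacement. Analyse the mediators and the CES-D by multiple imputation within arm, with baseline CES-D, ATQ-N, EROS and GSES in the imputation model, or by full-information likelihood. Show the baseline-replacement result only as a sensitivity analysis, and do not describe it as conservative for this analysis.

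The cost is slightly more programming and a missing-at-random assumption for this secondary analysis. No new data are needed, and the primary analysis and sample size stay as they are.

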## Background

Across the countries of the Organization for Economic Co-operation and Development (OECD), more than one in ten adults is involved in non-professional, typically unpaid, caregiving, defined as providing help with personal care or basic activities of daily living to people (family or friends) with functional limitations [1]. However, caring for a dependent family member involves emotional consequences for caregivers [2], and can adversely affect their mental health. In fact, it has been found that between 18 % and 48.3 % of caregivers have elevated depressive symptoms [3, 4] and 8.9 % meet the criteria for a major depressive episode [5].

Given their vulnerability, various programs of psychological intervention have been developed for caregivers [6, 7], especially for those with depressive symptoms [8]. However, despite the evidence that having subclinical depressive symptoms is a predictor of developing depression [9], there are only two randomized controlled trials [10, 11] aimed at preventing depression in caregivers with high levels of symptoms that have not yet developed the disorder (i.e., indicated prevention [12]). These interventions achieved a significant reduction in depressive symptoms, but were applied face to face, and face-to-face interventions, pose accessibility barriers to caregivers. Many caregivers cannot participate in face-to-face interventions due to difficulties such as time constraints, lack of financial resources, lack of available and geographically accessible support services, transportation problems, and problems finding a substitute caregiver to the care for the familiar or stigmatization.

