### Participants, recruitment and eligibility criteria

Participants will be recruited from the Official Register of Caregivers of the Ministry of Labor and Welfare of the Galicia Regional Government in northwestern Spain. A random sample of caregivers stratified by area type [rural (<2000 inhabitants) or urban (≥2000 inhabitants)] and province (Coruña, Lugo, Pontevedra or Orense) will be selected. Previously we have determined that approximately 39 % and 44 % of caregivers have elevated depressive symptoms [10, 11] and 8.9 % have depressive episodes [5]. As a result, to achieve the estimated sample size of approximately 180 participants we will need to randomly select approximately 550 caregivers for a screening prior to the verification of the eligibility criteria.

Caregivers will be contacted by mail and invited to participate in the study. They will be asked to return a stamped postcard if they do not want to be contacted further. Caregivers who do not return that card will be contacted with a brief description of the study. Those who are interested will undergo a screening to assess depressive symptoms and history of depressive episodes. Those who meet the initial selection criteria will be invited to participate in a longer evaluation that will evaluate the inclusion and exclusion criteria.

To be enrolled in the study, participants must meet the following inclusion criteria: (a) be officially recognized by the authorities as caregivers for a relative in a situation of dependency, (b) have a telephone, (c) obtain a pretreatment score ≥ 16 in the Center for Epidemiologic Studies Depression Scale (CES-D [25]), (d) not meet the DSM-IV criteria for a major depressive episode [26], (e) not have a history of major depression, (f) give informed consent. We will exclude those subjects that at the time of the assessment: (a) have been receiving psychological or pharmacological treatment for the last two months, (b) experience other conditions that could act as confounders in the study (e.g., symptoms due to the direct physiological effects of a substance or a medical condition), (c) have medical and mental disorders of such severity that they require immediate intervention (e.g., suicidal ideation) or that would make it impossible to participate in the study (e.g., severe hearing impairment), (d) care for a family member that has a terminal diagnosis, (e) are planning to institutionalize the family member or to move.

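### The CES-D analysis uses the pre-treatment score as an outcome level and not as a covariate, which costs precision; baseline adjustment of the incidence comparison would bring a smaller gain

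*Protocol article*

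**What the plan says.** The Statistical analyses section of the protocol article names its methods. For the primary outcome, cumulative incidence is calculated in each group, and then "The relative risk (RR) and number needed to treat (NNT) will be calculated" from published formulas. A survival analysis is added without a named model. For CES-D, a secondary outcome, "The effect of the interventions on depressive symptoms will be examined by using mixed factorial analysis of variance (ANOVA) tests with repeated measures".

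The Design section counts pre-treatment as the first of six measurement points in all three groups, and Table 1 lists CES-D at all six. Every participant has the baseline score because entry requires that they "obtain a pretreatment score ≥ 16 in the Center for Epidemiologic Studies Depression Scale". The Background states that "having subclinical depressive symptoms is a predictor of developing depression". The Randomization section describes no stratification by CES-D. Apart from entry and the repeated measures, the only stated use of baseline scores is to replace missing values.

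**The concern.** A baseline measurement of the outcome can enter a repeated-measures analysis in two ways: as one of the repeated outcomes, or as a covariate for the later ones. With six measurement points that include pre-treatment, a mixed factorial ANOVA takes the first way, and the arm effect is read from the group-by-time contrast, that is, from change since baseline. Subtracting the whole baseline score removes too much when the pre-post correlation is moderate, and it adds noise.

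What is at stake is precision. The contrast most exposed is probably CBC against BAC. The Background hypothesises that the two interventions differ, while the Discussion expects similar results, so any difference there may be small.

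For incidence, a crude comparison leaves unused a score that may carry prognostic information.

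**Working it through.** **The plan's own figure.** The Sample size section holds that "a sample size of 56 participants per group (168 in total) will be sufficient". Its target is a gap of 19 percentage points in incidence, at a significance level of .05 and 80 % power. The two underlying rates are not given. With the two-sided pooled formula at assumed rates of 25 % and 6 % (mean .155):

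n = [1.960 × √(2 × .155 × .845) + 0.842 × √(.25 × .75 + .06 × .94)]² / .19² = (1.003 + 0.416)² / .0361 = 55.8, so 56.

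Other pairs of rates also give 56 under other formulas (for example 26 % and 7 %, unpooled), so this pair is an assumption. Attrition of 5 to 8 % gives 56/.95 = 59 to 56/.92 = 61, which agrees with about 60. None of this relies on baseline adjustment.

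**CES-D, one post-treatment visit.** Let rho be the pre-post correlation, with equal variances. The document gives neither. In units of the outcome variance:

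- change from baseline: 2(1 − rho)
- baseline as covariate: 1 − rho²
- ratio: (1 − rho²) / [2(1 − rho)] = (1 + rho)/2

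| Assumed rho | Change | Covariate | Ratio | Change design needing the same precision as 60 per arm with the covariate |
|---|---|---|---|---|
| .3 | 1.40 | .91 | .65 | 60/.65 = 92 per arm |
| .4 | 1.20 | .84 | .70 | 60/.70 = 86 per arm |
| .5 | 1.00 | .75 | .75 | 60/.75 = 80 per arm |
| .6 | .80 | .64 | .80 | 60/.80 = 75 per arm |

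If the variances differ, the change variance exceeds the covariate variance by (SD pre − rho × SD post)², which is never negative. The direction therefore does not depend on equal variances, but the ratios in the table do. Selecting on CES-D ≥ 16 tends to lower rho. Replacing missing scores with baseline tends to raise it, which shrinks the gain.

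**CES-D, mean of the five post-baseline visits** (compound symmetry assumed). The variance of the mean is (1 + 4 rho)/5. The change variance adds 1 − 2 rho; the covariate variance subtracts rho².

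- rho .3: .35/.84 = .42
- rho .5: .35/.60 = .58
- rho .7: .27/.36 = .75

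**Incidence**, 25 % against 6 %, 56 per arm. Crude standard error: √[(.1875 + .0564)/56] = .0660. Power: Φ(.19/.0660 − 1.96) = .821. This is slightly above .80 because the standard error here is unpooled. The large-sample variance of the baseline-standardised risk difference, relative to crude, is:

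| Assumed odds ratio per SD of baseline CES-D | Variance ratio | Power |
|---|---|---|
| 1.0 | 1.00 | .821 |
| 1.5 | .98 | .828 |
| 2.0 | .95 | .841 |
| 2.5 | .91 | .855 |

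**Chance imbalance and the crude risk difference.** With 60 per arm, the SD of the standardised baseline difference is √(2/60) = .18, and its 95 % limit is 1.96 × .18 = .36 SD. At that limit the crude risk difference shifts by about .02 to .04 for odds ratios of 1.5 to 2.5, and by nothing if baseline is not prognostic. The planned difference is .19.

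**The case against.** The strongest reply is that both stated analyses are valid, so this is a preference for a more efficient method, and for CES-D it concerns a secondary outcome. That stands, and it limits the weight of the point. The method is nevertheless stated, and a better one is available from data already collected.

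Four stronger readings are tempting, and the document supports none of them.

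- *The CES-D analysis ignores baseline or leaves imbalance uncorrected.* It does neither: a group-by-time contrast subtracts the full baseline difference.
- *A group main effect over six levels would be diluted by the pre-treatment level.* The article does not say that the main effect will be read, and the interaction is the usual test in this design.
- *Baseline CES-D is the strongest measured predictor of onset.* The Background says only that subclinical symptoms predict depression. Whether the score is prognostic within a sample restricted to CES-D ≥ 16, without current or past major depression, is not shown.
- *The survival analysis omits the covariate.* No model is named, and an article may leave its covariates to the analysis plan.

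Two further objections bear on the remedy. Dropouts count as episodes: 5 to 8 % of 60 is 3 to 5 people, against 6 % of 60, or 3.6, expected episodes in an intervention arm. Baseline CES-D need not predict dropout, so the incidence gain shown is probably optimistic, and events are sparse for an adjusted model. Also, a model fitted to observed scores only would change the missing-data handling. Both are fair, and the fix below allows for them.

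**Conclusion.** The point holds as one of efficiency, not bias, and CES-D carries most of it. Using the pre-treatment score as a covariate would cut the variance of a single-visit contrast by 20 to 35 % at rho .6 down to .3, which makes the standard error 11 to 19 % smaller. This rests on an assumed rho, on equal pre and post variances, and on the natural reading that pre-treatment is a level of the time factor.

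For incidence, the crude relative risk and NNT are sound under randomisation. Adjustment is a minor gain that depends on the assumed rates and odds ratios. The sample size is not put in question.

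**What to change.** **Symptoms.** Replace the mixed factorial ANOVA by a repeated-measures model of the five post-baseline CES-D scores with arm, visit, arm-by-visit and baseline CES-D as covariate. Report the arm contrast at each visit. Keep the stated rule for missing scores unless it is changed separately and on its own merits.

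**Incidence.** Keep the crude rates, relative risk and NNT. Beside them, prespecify a risk difference and relative risk adjusted for baseline CES-D, using standardised risks from a logistic model or a simple model with robust errors, and derive an NNT from the adjusted risk difference. Keep the stated rule that dropouts count as episodes. With few events expected in the intervention arms, make baseline CES-D the only added covariate and name a fallback in case the model does not converge.

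**Cost.** Analysis wording only: the covariate is already collected and the models run in standard software. The small downside is sparse-event instability in the adjusted incidence model, which is why the crude results stay. Fixing the covariate before outcome data are seen also prevents its being chosen afterwards.
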